## Overview

Many Canadians receive a manual wheelchair (MWC) to address mobility impairment, yet they experience restricted social participation and mobility because they are not provided with the *skills* to independently, safely, and effectively use their MWC. Low self-efficacy, or a lack of *belief* in one's ability to use a MWC, can further compromise participation. Suboptimal use of a MWC results in substantial social costs such as reduced engagement in meaningful activity, social isolation, higher caregiver burden, and a poor use of financial resources considering the cost of MWC acquisition and attendant care. Access to comprehensive *wheelchair training* is constrained by the expense and limited availability of skilled therapists; demands of patient and/or clinician travel; lack of training opportunities when returning to the community. In addition, current Government of Canada, Public Health Agency of Canada (PHAC), and provincial health authority restrictions and guidelines related to the ongoing coronavirus (SARS-CoV-2) pandemic, including physical distancing and promotion of non-contact services, have compromised in-person wheelchair service delivery, in part because this is a vulnerable population with underlying medical conditions that are at increased the risk of developing severe complications from COVID-19. *Training to Enhance Adaptation and Management for Wheelchair users* (TEAM Wheels) is a 4-week, community-based, tailored *eHealth* program integrating peer-led and independent home training components to optimize learning while limiting the time demands of health care professionals and mitigating the risk of COVID-19 for participants, peer-trainers, and research staff. The *eHealth* program is delivered using a 10" computer tablet with a custom home-training application and a secure teleconferencing application. The tablet mounts conveniently on the wheelchair user's lap for "in-chair" training, enabling MWC users to learn and practice mobility skills in authentic contexts of home and community. The interactive home-training application includes a structured curriculum with over 200 video clips featuring education, peer demonstration, and training activities. *eHealth* offers the convenience of autonomy over training schedules and reduced demand for outpatient visits that provides a supportive physical distancing, non-contact approach. The peer-led teleconferencing component involves experienced MWC users with specialized training and lived experience who can leverage their own experience and ability to relate as influential peers. The peer trainer conducts 3 real-time, web-based video conferencing sessions using the Microsoft (MS) Teams cloud platform via the same computer tablet. Individualized goals are negotiated, introducing wheelchair skills and management strategies, and providing an orientation to the *eHealth* home program. Peer trainers monitor *eHealth* training activity, which the tablet uploads to a secure website, intervening or modifying the program when required. Additional communication can be initiated between MWC user and peer trainer using a messaging function of MS Teams on the computer tablet.

## Background and Significance

**Demand for MWC use in Canada is common and growing.** In 2016, Giesbrecht and Miller reported that close to 200,000 community-dwelling Canadians use a MWC; the number of wheelchair users has risen by 30% over the previous ten years. Chronic conditions, which increase with age, are often predisposing factors for use of a wheelchair, including cardiovascular disease (e.g., stroke and amputation secondary to diabetes), multiple sclerosis, arthritis, and neuromuscular diseases. An aging Canadian population suggests the number of MWC users will grow substantially in the coming years.

**Challenges to both the individual and health care system.** MWC users experience restricted participation, mobility, and quality of life. **Giesbrecht** and **Miller** recently reported that among persons with a disability, wheelchair users were more likely to experience home accessibility issues; require assistance with more activities of daily living on a more frequent basis; and have greater out-of-pocket expenses to obtain assistance. In Canada, over 95% of MWC users required caregiver assistance with at least one major life activity including 37% for basic mobility. Restricted mobility is associated with reduced participation and social connectedness, leading to isolation, stress and low self-esteem impacting quality of life. Stroke survivors adjusting to MWC use identified substantial restriction in *caregivers'* social roles and increased burden of care; these are typically family members or unpaid individuals. In Canada, the **annual** incidence of tips/falls is 5.2%, with 4.2% resulting in injury and 2.5% requiring an ER visit. In the US, wheelchair-related accidents result in **1 death per week**.

Infection prevention and control (IPC) measures are based on federal, provincial, and local epidemiological evidence tailored to the local context and based on a public health ethics framework. The evidence-based infection prevention and control guidelines and recommendations from PHAC, including physical isolation and distancing, aimed at lowering the incidence of exposure and SARS-CoV-2 (coronavirus; COVID-19) infection, compound a MWC user's isolation and access to outpatient health care providers, transportation, community, employment, and personal support persons. Telephone, web-based, or other means of telecommunication technology are recommended to be used to conduct virtual assessments and communication when in-person assessment is not necessary.

**Issues related to MWC use can be redressed through MWC skills training, but typically are not.** Two recent systematic reviews of structured MWC skills training programs found them to be safe, practical and effective; several RCTs report significant and clinically meaningful improvement in skill capacity during inpatient rehabilitation and in the community. However, training is typically delivered by a physical or occupational therapist and requires 4 to 8 sessions; at least 10-12 hours of training is recommended to ensure safe and proficient performance. During a hospital stay, when most MWCs are prescribed, competing discharge demands are often prioritized over training. **Best, Routhier** and **Miller**, in a survey of 68 Canadian rehabilitation centres, reported over half of therapists spent two hours or less on wheelchair-related training and 18% provided no training. Funding for community-based services has been in decline and is insufficient to support therapist-intensive training either before or after discharge. Time and travel demands for MWC user and therapist make traditional training cost-prohibitive. Long wait lists and inaccessibility of rehabilitation services, particularly in rural areas, further exacerbate the problem. In light of the SARS-CoV-2 pandemic that began in Canada in March 2020, strategies and recommendations for at-risk populations to prevent infection also complicate face-to-face delivery of health services, including MWC training. Recommendations to self-isolate and practice physical distancing, maintaining clean hands, hand rims, and wheelchair, and avoidance of in-door/out-door community settings with large crowds are among these complicating factors. The World Health Organization (WHO) states that "People with disability may also be disproportionately impacted by the outbreak because of serious disruptions to the services they rely on. The barriers experienced by people with disability can be reduced if key stakeholders take appropriate action". Training is ideally delivered early in the transition to MWC use. New users (defined in the literature as < 1 year) have shown significantly larger improvements with structured training; however, length of use is not correlated with skill capacity (Lemay et al., 2012) and comparable training benefits have been

demonstrated among experienced MWC users. Some data suggest females have lower initial self-efficacy and may require more practice for advanced skills; however, structured training has proven beneficial for both sexes. Likewise, the *application* and *clinical benefits* of training are applicable across diagnoses. Meta-analyses of MWC skills training have demonstrated significant differences and a large effect size (SMD = 2.0) across studies among heterogeneous participant samples, and sub-analysis found no significant interaction for diagnosis.

**Health care is changing and disruptive strategies are necessary.** Alternative and disruptive rehabilitation approaches are required that are clinically effective, cost-effective, COVID-19 pandemic focused, and sustainable. Two strategies demonstrate the potential to reduce burden on the healthcare system: (1) delivery in the community via *eHealth* and (2) use of peer trainers. These approaches are compatible and synergistic, providing an opportunity to ameliorate training issues among MWC users in a way that is cost-effective; delivered at the most appropriate time (i.e. post-discharge) and in the most appropriate context (i.e. participant-centered, within community, mitigating COVID-19 infection risk); and in a way that is sustainable. Moreover, they integrate important theoretical precursors known to influence behaviour, in this case wheelchair use and social participation. *eHealth* and peer training can cultivate psychological needs identified by Self-Determination and Social Cognitive theories.

A peer, who has experiential knowledge and similar characteristics as the target population, can cultivate social connections through sharing of realized knowledge. Peer-led training is feasible to administer and effectively improves wheelchair skills, self-efficacy, and satisfaction with participation. Providing *eHealth* training at home fosters autonomy (i.e., choice and volition), while peers enhance feelings of competence (i.e., self-efficacy) and relatedness (i.e., feeling connected). When these three needs are satisfied, autonomous motivation (i.e., engaging in an activity by choice) increases, driving behaviour change and maintenance, such as wheelchair use and social participation. Every province and territory in Canada has implemented delivery of *eHealth*, providing potential partnership opportunities for TEAM Wheels. By integrating a peer-led approach with the *eHealth* training program, we are leveraging two novel strategies. This is a contemporary approach to community rehabilitation with MWC users that builds on innovations we have already developed in Canada. The results of this trial will provide evidence to move forward with implementation of service at the regional health care delivery level. Furthermore, access to TEAM Wheels has the potential for future exploration in the context of rural and remote service delivery, where consumers have even greater restriction to health care access.

**Purpose.** Our purpose is to *evaluate the effect* of a 1-month, peer-led *eHealth* training program (TEAM Wheels) on satisfaction with activity participation and related rehabilitation outcomes among individuals transitioning to MWC use, compared with current wheelchair training practice.

**Hypotheses:** We hypothesize that at post-treatment, the primary outcome of wheelchair-related participation will be significantly higher in the TEAM Wheels group and that post-treatment improvements will be retained at 6-month follow up. We also hypothesize that the TEAM Wheels program will demonstrate clinically and statistically significant differences at post-treatment and at 6-month follow up on secondary outcome measures of wheelchair-specific self-efficacy; skill capacity and performance; health-related quality of life; and objective measurement of mobility.

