**Objectives:****Primary Objectives: Participation**

1. To measure the effect of TEAM Wheels on *satisfaction with participation* in important activities of life compared to current practice;
2. To measure retention of participation benefits at 6-months post treatment.

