## Methods:

**Research Design.** This RCT employs 3 sites (Vancouver, Winnipeg, Quebec City) comparing a 4-week MWC training intervention and wait-list control group among individuals transitioning to MWC use. TEAM Wheels will be delivered in the community specifically targeting new users, defined in the literature as individuals within one year of receiving their MWC.

**Methods.** Participants will be randomly assigned to the TEAM Wheels or control group using a 1:1 allocation ratio between groups. To support balance between groups and masking of assignment, our statistician ([name]. – Quebec City) will create a computerized randomization process with undisclosed block size. Randomization will be stratified by site to ensure comparable treatment group size ( $n \sim 18$  per site). Given the potential benefits of the intervention already reported in our previous studies, control group participants will also receive the TEAM Wheels intervention following a 4-week control period and post-treatment data collection (they will be on a “wait-list” for the TEAM Wheels program and receive **no intervention** during the study period).

Following enrolment, baseline data will be collected and entered into a secure MS Teams database. MS Teams data storage is approved by the University of Manitoba Health Research Ethics Board (HREB) and is *Personal Health Information Act* (PHIA)/*Freedom of Information and Protection of Privacy Act* (FIPPA) compliant. The site Research Assistant (RA) will then obtain the participant’s group assignment and coordinate timing for the first teleconference peer trainer session conducted via the computer tablet; for treatment group assignments this will occur as soon as is practical and for control group assignments this will be scheduled after blinded post-treatment data collection is complete. The Research Assistant will also arrange blinded follow-up (retention) data collection for treatment group participants 6 months after post-treatment data collection. Although collecting 6-month retention data for the control group would be optimal, delaying a potentially beneficial intervention and the associated risk of participant attrition make this option undesirable.

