During the coronavirus pandemic and associated restrictions, researchers will not be conducting home visits, having participants come in for visits, or meeting in public/community areas. In addition, infection prevention and control practices will be implemented. All study equipment loaned to study participants will be sanitized/disinfected prior to sending it out as well as when the equipment is returned to the research team. This will be done according to the Government of Canada recommendations for preparing/choosing hard-surface disinfectants, including (1) preparing a fresh solution using bleach with a concentration of 5% hypochlorite and combine in a 5 mL bleach: 250 mL water ratio, (2) using medical grade disinfectant wipes, (3) using an alcohol-based solution with a minimum 70% ethanol or isopropyl alcohol concentration. The RA responsible for disinfecting the equipment will be trained in the proper handling and use of cleaning products and disinfecting/sanitizing procedures and will be provided and expected to wear the recommended personal protective equipment (PPE), including non-medical mask and gloves, during the sanitization processes. Post-treatment data will be collected at week 7 to incorporate a 1-week window for consolidation of learning following the 4-week intervention. Follow-up (retention) data will be collected from the TEAM Wheels group participants 6 months later (week 31).

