### **Study Sites.**

The three study sites offer varied provincial approaches to MWC procurement as well as differences in geography, culture and climate, and provincial COVID-19 recommendations and guidelines (Phase of restrictions) to prevent infection. This diversity allows TEAM Wheels delivery in multiple contexts; site-specific post-hoc analyses may provide additional insights. Sites are major urban centres with access to a large number of MWC users. In Manitoba, approximately 1800 MWCs were distributed to first-time users in 2016, primarily within Winnipeg (pop ~700,000). The population of Quebec City is comparable and Vancouver is over three times as large, providing a sizable pool of potential participants.

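### A 6-month hypothesis of significant differences has no 6-month comparison behind it: only the treated arm is measured then, and the planned time test does not isolate retention

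*Protocol*

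**What the plan says.** **Hypotheses (Protocol, Background and Significance).** For the primary outcome, the WhOM, the 6-month claim is that "post-treatment improvements will be retained at 6-month follow up". For the secondary outcomes (self-efficacy, skill capacity and performance, health-related quality of life, measured mobility) the claim is stronger: the program will demonstrate "clinically and statistically significant differences at post-treatment and at 6-month follow up on secondary outcome measures".

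**Objectives.** The second primary objective is "To measure retention of participation benefits at 6-months post treatment". The second secondary objective is worded in the same way. Comparison with current practice appears only in the first item of each list.

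**Who is measured (Methods).** The design paragraph provides for "blinded follow-up (retention) data collection for treatment group participants 6 months after post-treatment data collection". The Assessments paragraph repeats it: "Follow-up (retention) data will be collected from the TEAM Wheels group participants 6 months later (week 31"). The Outcome measures paragraph also confines the 6-month questionnaires to treatment group participants. Controls are wait-listed and receive TEAM Wheels once post-treatment data are in, at week 7.

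**The acknowledged trade-off.** The design paragraph begins a sentence with "Although collecting 6-month retention data for the control group would be optimal" and then gives two reasons for not doing so: it would delay a potentially useful intervention, and it would risk attrition.

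**Analysis (Data Analysis).** Groups are compared on change over time with a GLM. For 6 months the only method named is a repeated-measures ANOVA in the treatment group, to evaluate retention.

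**The concern.** One sentence applies the word differences to two time points. At post-treatment it has a randomised comparison behind it. At 6 months it has none. The sentence says that the program will demonstrate the differences, and the stated purpose of the trial is an effect relative to current practice, so the natural reading is comparative and causal at both times. Nothing later in the protocol narrows it.

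Two consequences follow. First, a stated hypothesis cannot be tested as written. A significant time effect in the treated arm would appear to satisfy it, although such an effect can arise from any change over time. Second, the overall test of time across three visits asks whether the three means are all equal. Retention concerns a single contrast, week 7 against week 31. The results are meant to inform regional implementation, so what may be claimed about durability matters.

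**Working it through.** **1. The passages side by side**

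| Time point | Treated arm | Control arm | Named analysis | Hypothesis on secondary outcomes |
|---|---|---|---|---|
| Baseline | measured | measured | | |
| Week 7 | measured | measured, still untreated | GLM between groups | significant differences |
| Week 31 | measured | not measured, already offered the program | repeated-measures ANOVA, treated arm only | significant differences |

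The week-31 row has no control observations, so no between-group estimate or test exists whatever the sample size. Adding a control visit at week 31 would not repair this, because controls have crossed over by then.

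**2. The protocol's own sample size**

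Inputs (Sample Size): f = 0.45, correlation 0.6, alpha 0.05, power 90%, stated N = 42. For a between-factors repeated-measures ANOVA the noncentrality is λ = f²·N·m / (1 + (m − 1)ρ), with 1 and N − 2 degrees of freedom and m measurements.

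- m = 2, N = 42: λ = 0.2025 × 42 × 2 / 1.6 = 10.63, power 88.9%. The smallest balanced N for 90% is 44.
- m = 3: the smallest balanced N for 90% is 42.

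The figure reproduces exactly or within two participants. It concerns a comparison between groups and gives no support to a 6-month claim in one arm.

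**3. Does the overall time test isolate retention?**

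For n treated participants, visit SD σ and correlation ρ between visits, the time test has λ = n·Σ(μⱼ − μ̄)² / [σ²(1 − ρ)], with 2 and 2(n − 1) degrees of freedom. Inputs: ρ = 0.6; n = 21 (42/2) or 27 (54/2); week-7 gain d = 0.93 SD (Outcome measures). Assumptions: equal variances, equal correlations, and 0.93 taken in units of the visit SD, since the protocol does not say which SD was used.

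- Gain fully kept, means (0, d, d): Σ = (2/3)d² = (2/3)(0.8649) = 0.5766.
- Gain fully lost, means (0, d, 0): Σ = (2/3)d² = 0.5766.

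The two are identical. With n = 21, λ = 21 × 0.5766 / 0.4 = 30.27, and the test is significant with probability 99.9% in either case. With n = 27, λ = 38.92 and the probability exceeds 99.9%. A significant result therefore cannot tell complete retention from complete loss.

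**4. What the direct contrast would give**

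The 95% CI for week 31 minus week 7 has half-width t·σ·√[2(1 − ρ)/n]. Implied σ = 2.3/0.93 = 2.47 WhOM points, under the same assumption about the SD.

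- n = 21: 2.086 × 2.47 × √(0.8/21) = 1.01 points.
- n = 27: 2.056 × 2.47 × √(0.8/27) = 0.87 points.

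Both are below the 1.6 points that the protocol cites as clinically meaningful, so the contrast is informative at the planned size.

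**5. Illustration of the attribution problem**

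Assume no program effect and a background drift of δ SD units from baseline to week 31. A two-sided paired t test at 0.05 has noncentrality δ√n / √[2(1 − ρ)]. The drift sizes are assumptions; the protocol gives none.

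| Drift (SD) | n = 21 | n = 27 |
|---|---|---|
| 0.2 | 16% | 20% |
| 0.3 | 31% | 39% |
| 0.5 | 68% | 80% |

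The nominal rate is 5%. The protocol does not name this paired test; it stands in for any comparison with baseline in one arm.

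**The case against.** **The design is open about the choice.** Single-arm follow-up is stated in several places and justified. That stands: the decision not to hold controls back for 6 months is a reasoned trade-off and is not criticised here.

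**Only one sentence overreaches.** The objectives and the primary-outcome hypothesis claim retention and nothing more. That also stands, and it limits the point. They share the attribution limit but do not contradict the design.

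**Differences could mean change from baseline.** On that reading the hypothesis is testable. The same word covers post-treatment, though, where the analysis is between groups, and even as within-arm change it cannot be credited to the program.

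**The false-positive rates depend on an assumed drift and an unnamed test.** Correct. The protocol gives no background drift and says that length of use is not correlated with skill capacity, which weakens an adaptation argument for skills. The rates show direction only.

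**Stronger readings that a reader might infer.** One is that easing pandemic restrictions or the opposite season at week 31 would push scores up. The documents do not support a common shift. Recruitment is staggered over an estimated 12 months, so participants would move between seasons in both directions. Guidelines are described as ever-changing, not easing. Study Sites mentions "differences in geography, culture and climate, and provincial COVID-19 recommendations and guidelines" as differences between sites, not as a trend over time. These are possible sources of background change and no more. Another is that N = 42 counted a 6-month visit in both arms, because three measurements reproduce it exactly. The number of measurements is not stated, and two measurements come within two participants.

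**Conclusion.** The point holds as a mismatch between a hypothesis and the design. A between-group 6-month difference on the secondary outcomes is not testable, and this follows from the visit schedule with no numerical assumption. Within-arm change at week 31 cannot be attributed to the program. The named ANOVA, read as its overall time test, does not measure retention: full retention and full loss give it the same noncentrality, and that equality holds for any d, n, σ and ρ under equal variances and correlations. The 99.9% and the CI half-widths of 0.87 to 1.01 points rest further on 0.93 and 2.47 being in visit-SD terms and on a correlation of 0.6.

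The randomised week-7 comparison is unaffected. The documents do not support calling the single-arm follow-up an undisclosed flaw, or any particular size of false-positive rate at 6 months. The change should be made, because it alters what the trial may conclude at almost no cost.

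**What to change.** 1. **Hypotheses.** Remove the 6-month time point from the secondary-outcome sentence on differences, or reword it as retention of post-treatment change within the TEAM Wheels group.
2. **Data Analysis.** For primary and secondary outcomes, estimate retention as week 31 minus week 7 in the treated arm with a 95% CI. The three-visit ANOVA may stay as supporting description.
3. **Interpretation.** State that the 6-month data are uncontrolled, that change after week 7 may include background change, and that between-group claims and the word effect apply to week 7 only.

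The retention objective can remain where it is once it is read this way; moving it to secondary, or tabulating calendar month and restriction phase, is a matter of preference.

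**Cost.** Protocol wording only: no extra visit, participant or delay for controls. The sponsor gives up a 6-month efficacy claim that the design cannot support.
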